|----------------------------------------|---------------------------------------------------------------------------------------------------------------------------------------------------------------------------------------------------------------------------------------------------------------------------------------------------------------------------------------------------------------------------------------------------------------------|
|                                        | 
Primary safety endpoint
 
 
1. Number and occurrence of related SAE and Grade 3 AE from time of first administration of ivermectin until the end of the study
 
 
Secondary safety endpoint
 
 
1. Number and occurrence of any AE from time of first administration of ivermectin until the end of the study
 
 |
| Data and Safety Monitoring Plan | Participants will be treated when criteria to initiate a rescue treatment are reached or at the end of the active study follow-up period (D7).                                                                                                                                                                                                                                                                      |

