### 4.2.2. Secondary objectives

- To compare efficacy of ivermectin 200 $\mu$ g/kg single dose versus two-day 200 $\mu$ g/kg treatment versus three-day 200 $\mu$ g/kg treatment versus three-day 300 $\mu$ g/kg treatment
- To compare efficacy of ivermectin three-day 300 $\mu$ g/kg treatment compared to placebo
- To compare safety and tolerability of ivermectin 200 $\mu$ g/kg single dose versus two-day 200 $\mu$ g/kg treatment versus three-day 200 $\mu$ g/kg treatment versus three-day 300 $\mu$ g/kg treatment
- To compare safety and tolerability of ivermectin three-day 300 $\mu$ g/kg treatment compared to placebo

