### **8.3. Primary Safety Endpoint**

1. Number and occurrence of related SAE and Grade 3 AE from time of first administration of ivermectin until the end of the study

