### **8.4. Secondary Safety Endpoint**

1. Number and occurrence of any AE from time of first administration of ivermectin until the end of the study

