### 12.1. Definitions

**Adverse Event (AE):** An AE can therefore be any unfavourable and unintended sign (including an abnormal laboratory finding), symptom or disease temporally associated with the study, whether or not considered related to the study interventions.

**Adverse Reaction (AR):** An AR is any untoward or unintended response to ivermectin. This means that a causal relationship between ivermectin and/or *Plasmodium* infection and an AE is at least a reasonable possibility, i.e., the relationship cannot be ruled out. All cases judged by either the reporting medical investigator or the sponsors as having a reasonable suspected causal relationship to ivermectin and/or *Plasmodium* infection will be qualified as adverse reactions.

**Unexpected Adverse Reaction:** An unexpected adverse reaction is where the nature or severity of the adverse reaction is inconsistent with that expected for the intervention.

**Serious Adverse Event (SAE):** To ensure no confusion or misunderstanding of the difference between the terms "serious" and "severe", which are not synonymous, the following note of clarification is provided: The term "severe" is often used to describe the intensity (severity) of a specific event (as in mild, moderate, or severe myocardial infarction); the event itself, however, may be of relatively minor medical significance (such as severe headache). This is not the same as "serious," which is based on Participant/event outcome or action criteria usually associated with effects that pose a threat to a participant's life or functioning. Seriousness (not severity) serves as a guide for defining regulatory reporting obligations.

An SAE is an adverse event that results in any of the following outcomes:

- death;
- a life-threatening adverse event;
- inpatient hospitalization or prolongation of existing hospitalization;

- a persistent or significant disability/incapacity;
- a congenital anomaly/birth defect.

`Life threatening` refers to an adverse effect that at occurrence represented an immediate risk of death to the participant; it does not refer to an event that hypothetically might have caused death if it were more severe. Similarly, a hospital admission for an elective procedure is not considered a Serious Adverse Event.

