### **12.3. Reporting procedures for AEs (Excluding SAEs)**

All AEs occurring during the study, since the signature of the Informed Consent Form until the end of the follow up period, observed by the investigator or reported by the participant will be recorded in the CRF. Malaria events occurring at any time during the study will be recorded as an AE.

AEs that result in a participant's withdrawal from the study or that are present at the end of the study will be followed up (if participant's consent to this) until a satisfactory resolution or stabilization occurs, or until a non-study related causality is assigned.

**Grade 1** Mild: Transient or mild discomfort (< 48 hours); no medical intervention/therapy required;

**Grade 2** Moderate: Mild to moderate limitation in activity - some assistance may be needed; no or minimal medical intervention/therapy required;

**Grade 3** Severe: Marked limitation in activity, some assistance usually required; medical intervention/therapy required, hospitalization possible;

**Grade 4** Potentially life threatening: Extreme limitation in activity, significant assistance required; significant medical intervention/therapy required, hospitalization or hospice care probable.

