### **12.6. Safety hold of the study and stopping rules**

The study may be placed on safety hold for the following reasons

- On advice of the safety monitor;
- On advice of the investigators;
- On advice of the EC
- One or more participants experience a SAE that is determined to be related to the study product administration;
- One or more grade 3 or higher adverse events which are unexpected and possibly or probably related to the drug administration.

If the study is placed on hold it may only be restarted following discussion with and approval from the Safety monitor, the sponsor and study investigators.

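### The primary safety endpoint names Grade 3 adverse events but not Grade 4, so a non-serious Grade 4 event goes uncounted, and its start point is worded for ivermectin recipients only

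*Protocol*

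**What the plan says.** Protocol 8.3 defines the primary safety endpoint as "Number and occurrence of related SAE and Grade 3 AE from time of first administration of ivermectin until the end of the study". The endpoint list in the synopsis opens the same way: "Number and occurrence of related SAE and Grade 3 AE". The secondary safety endpoint in 8.4 is "Number and occurrence of any AE from time of first administration of ivermectin until the end of the study".

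Protocol 12.3 grades adverse events from 1 to 4. Grade 3 is "Severe: Marked limitation in activity, some assistance usually required; medical intervention/therapy required, hospitalization possible". Grade 4, the top of the scale, begins "Potentially life threatening: Extreme limitation in activity, significant assistance required" and describes admission to hospital or hospice as probable.

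Protocol 12.1 separates severity from seriousness. For the life-threatening criterion it requires that the risk of death was immediate, and adds that "it does not refer to an event that hypothetically might have caused death if it were more severe". Other SAE criteria are death, admission or a longer stay in hospital, lasting disability and congenital anomaly. A further clause lets important medical events be treated as SAEs on medical judgement.

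The safety-hold rule in 12.6 uses wider wording than the endpoint: "One or more grade 3 or higher adverse events which are unexpected".

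One of the secondary objectives in 4.2.2 opens "To compare safety and tolerability of ivermectin three-day" and goes on to name the 300 µg/kg regimen against placebo.

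**The concern.** Safety is the first primary objective listed in 4.2.1, and the synopsis gives the safety of the 3x300 µg/kg course as an aim of the study. An endpoint serving that aim should not count a severe event and omit a worse one of the same kind. As worded, a Grade 4 event has only one way in, as a related SAE, and Grade 4 does not by itself make an event an SAE. An event that meets no SAE criterion would therefore count if graded 3 but not if graded 4.

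It is also unclear whether the word related qualifies SAEs only or Grade 3 AEs as well. That decides how wide the gap is.

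The start of the counting window is a second, smaller fault. Arm IVb receives placebo and never ivermectin, so a window that opens at a participant's first ivermectin dose has no starting point there. Yet 4.2.2 asks for the comparison with that arm.

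**Working it through.** **1. The protocol's own safety figure.** The synopsis says five participants per escalation arm give a 95% probability of detecting an event of 50% prevalence. The check is 1 − 0.5^5 = 0.969, which agrees. It does not bear on this point, which concerns what counts as an event.

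**2. Does Grade 4 imply SAE?** Take the routes in 12.1 in turn.
- *Life-threatening:* the risk of death must be immediate. Grade 4 is only potentially life-threatening, so it does not automatically qualify.
- *Hospitalisation:* Grade 4 makes it probable, not certain. Section 9 already keeps participants in hospital for at least 72 hours and up to 7 days at their convenience, so a new admission cannot mark an event during dosing and a prolonged stay is hard to identify. Section 12.1 also excludes some stays, such as precautionary observation under 24 hours.
- *Important medical event:* this would take in many Grade 4 events, but it is permissive and rests on judgement.

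A Grade 4 event can therefore be non-serious. The scale itself sits in 12.3, whose heading covers AEs other than SAEs.

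**3. What 8.3 counts.** Reading A: related applies to both SAEs and Grade 3 AEs. Reading B: it applies to SAEs only.

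| Event | Reading A | Reading B |
|---|---|---|
| Grade 3, related, non-serious | counted | counted |
| Grade 4, related, non-serious | **not counted** | **not counted** |
| Grade 4, related, serious | counted | counted |
| Grade 3, unrelated | not counted | counted |
| Grade 4, unrelated, serious or not | not counted | **not counted** |

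Under A the inconsistency is confined to related, non-serious Grade 4 events. Under B it extends to unrelated Grade 4 events, including serious ones.

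**4. What one uncounted participant does.** Arm sizes are 17 (IVa) and 5 (I to III). The share is 1/17 = 5.9 percentage points, or 1/5 = 20 points. As an illustration, the one-sided 95% Clopper-Pearson upper bound with zero events is 1 − 0.05^(1/n). With one event it is the p that solves (1 − p)^n + n·p·(1 − p)^(n−1) = 0.05.

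| Arm size | 0 events | 1 event |
|---|---|---|
| 17 | 16.2% | 25.0% |
| 5 | 45.1% | 65.7% |

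The protocol plans no such bound. The table shows only how much one event matters at these sizes.

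**5. How likely is such an event?** The documents give no rate. If each participant had a probability q of a non-serious Grade 4 event (an assumption), the chance of at least one among n is 1 − (1 − q)^n.

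| q | Arm IVa, n = 17 | All ivermectin, n = 3×5 + 17 = 32 |
|---|---|---|
| 1% | 16% | 28% |
| 10% | 83% | 97% |

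Nothing in the protocol says where in this range, or below it, the true rate lies.

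**6. The window.** Read per participant, it is undefined for 17 of 34 randomised (50%) and 17 of 49 overall (35%). Against that reading, section 9 calls day 0 the day of ivermectin administration for all participants. The schedule in section 7 times a sample from the last ivermectin treatment without excepting placebo, and runs on hours after first dose. Section 4.1 makes assessments the same in all arms. Ivermectin is thus used loosely for study drug.

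**The case against.** The strongest defence is that the gap is narrow and nothing is lost from the trial. Grade 4 here means extreme limitation and substantial medical intervention, so many such events would qualify as SAEs through hospitalisation or the important-medical-event clause. The scale is functional and sets no laboratory cut-offs, so it does not by itself generate symptom-free Grade 4 findings. The any-AE endpoint in 8.4 would still count the event. The DSMB reviews all AEs and SAEs under section 12, and 12.6 already covers grades above 3. No safety test, threshold or sample size is tied to 8.3; section 5.1 calls the escalation arms descriptive and sizes Arm IV on efficacy.

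All of this stands, and it limits the consequence. It does not remove the fault, because the important-medical-event clause is discretionary. The secondary endpoint would report the event among AEs of every grade, and the primary result would still omit it.

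A reader might go further and infer that every placebo event falls outside the safety endpoints. The documents do not support that. The loose use of ivermectin elsewhere and the placebo comparison in 4.2.2 point to first study drug as the intended start, and 12.3 records AEs from consent in all participants. Reading the start as the trial's first ivermectin dose would also bring placebo events in. The window is badly worded; it does not exclude the arm.

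A reader might also infer that any event regraded from 3 to 4 leaves the count. That is too strong: a related serious Grade 4 event stays in under either reading of related.

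**Conclusion.** The point holds as a wording fault in the primary safety endpoint. Applied as written, 8.3 and the synopsis omit a related Grade 4 event that meets no SAE criterion while counting a related Grade 3 event. This follows from 12.1, 12.3 and 12.6 without any outside figure. It assumes only that the endpoint is applied literally and that some Grade 4 events are non-serious, which 12.1 allows.

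The size cannot be given as an expected bias. One uncounted participant is worth 5.9 points in Arm IVa or 20 points in an escalation arm, and whether there will be any is unknown. The bounds and probabilities above are illustrations, not predictions. Sample size, power and error rates are unaffected.

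The start of the window is literally undefined for the 17 placebo participants, but the intended meaning is probably clear. It needs correcting so that both randomised arms are counted from the same event.

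**What to change.** - In 8.3 and the synopsis, replace Grade 3 AE with *Grade 3 or higher AE*.
- In the same places, state whether related applies to SAEs only or to SAEs and AEs. The sponsor should confirm its intent. Applying it to SAEs only brings unrelated AEs of Grade 3 or higher into the primary endpoint, including any malaria episode of that grade, since 12.3 records malaria events as AEs.
- In 8.3, 8.4 and the synopsis, start the window at the *first administration of study drug (ivermectin or placebo)*.

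The cost is a short amendment to three places, best made before Arm IV is unblinded. No visit, sample or data item is added, because AEs in all arms are already recorded from consent. For a given reading of related, adding Grade 4 can only leave the primary safety count unchanged or raise it; a possible rise is the only downside.

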### **8.4. Secondary Safety Endpoint**

1. Number and occurrence of any AE from time of first administration of ivermectin until the end of the study

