| Treatment duration      | 
 
- One day ivermectin
 
- Two days ivermectin
 
- Three days ivermectin
 
- Three days placebo
 
                                                                                                                                                                                                                                                                                                                                                                                                                                                                                                                                                                                                                                                                                                                                                                                          |
| Follow-up duration      | 14 days (D1, D2, D3, D4, D5, D6, D7, D14)                                                                                                                                                                                                                                                                                                                                                                                                                                                                                                                                                                                                                                                                                                                                                                                                                                                                                                                     |

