#### 6.2.6. Rescue medication

The following circumstances warrant discontinuation of study treatment and the implementation of rescue medication

- Any parasitaemia based on microscopy with fever ( $>38.5^{\circ}\text{C}$ , observed by study team) post-dose
- Development of danger signs or severe malaria on any treatment day between Study Day 0 and Day 7 in the presence of parasitaemia
- Parasitaemia  $\geq 20,000$  parasites/ $\mu\text{l}$

The start of the rescue medication with artemether-lumefantrine may occur after the start of trial medications and up to Study Day 7 as deemed necessary by the investigator. Any

participants who would not need the rescue medication up to study Day 7, will be given artemether-lumefantrine at end of active follow-up (Day 7). The rescue medication according to the local guidance will be used to treat severe malaria.

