## **9. Duration of the study**

Participants have to be hospitalized for at least 72 hours or for up to 7 days, depending on their convenience. After discharge from the hospital, Participants will return daily to the Clinical Centre for further assessments during active follow-up until Day 7 and a final visit on Day 14. The duration of involvement in the study from day 0 (day of ivermectin administration) will be 14 days. The start of the trial is defined as the date of the first visit of the first participant. The end of the trial is the date of the last visit of the last participant.

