Important medical events that may not result in death, be life-threatening, or require hospitalization may be considered a serious adverse event when, based upon appropriate medical judgment, they may jeopardize the participant or require medical or surgical intervention to prevent one of the outcomes listed in this definition. Examples of such medical events include allergic bronchospasm requiring intensive treatment in an emergency room or at home, blood dyscrasias or convulsions that do not result in inpatient hospitalization, or the development of drug dependency or drug abuse.

The following situations do not constitute an SAE : i) hospitalization (including inpatient or outpatient hospitalization for an elective procedure) for a pre-existing condition that has not worsened unexpectedly; ii) hospitalization as a precautionary measure for continued observation or medical management for less than 24 hours, hospitalization for an individual who cannot tolerate oral medication or for hydration); iii) hospitalization to carry out a procedure programmed already before the participant`s participation in the study; iv) hospitalization for social reasons.

**Serious Adverse Reaction (SAR):** An adverse event (expected or unexpected) that is both serious and, in the opinion of the reporting investigator or sponsors, believed to be possibly, probably or definitely due to ivermectin or any other study treatments, based on the information provided.

**Suspected Unexpected Serious Adverse Reactions (SUSARs):** A SUSAR is a SAE that is unexpected and thought to be possibly, probably or definitely related to ivermectin.

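### The any-AE endpoint runs to Day 14 without a split, so events after the artemether-lumefantrine given by Day 7 are counted in the safety result for ivermectin

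*Protocol*

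**What the plan says.** The first primary objective (Protocol 4.2.1) is the safety and tolerability of ivermectin.

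- **Secondary safety endpoint (8.4):** "Number and occurrence of any AE from time of first administration of ivermectin until the end of the study". It has no relatedness condition.
- **Primary safety endpoint (8.3):** "Number and occurrence of related SAE and Grade 3 AE from time of first administration of ivermectin until the end of the study".
- **Length of follow-up (section 9):** "The duration of involvement in the study from day 0 (day of ivermectin administration) will be 14 days".
- **Second drug (6.2.6):** "The start of the rescue medication with artemether-lumefantrine may occur after the start of trial medications and up to Study Day 7", and the remaining "participants who would not need the rescue medication up to study Day 7, will be given artemether-lumefantrine at end of active follow-up (Day 7"). The Synopsis agrees: "Participants will be treated when criteria to initiate a rescue treatment are reached or at the end of the active study follow-up period (D7").
- **Relatedness (12.2):** an event is intervention-related if its link to the study intervention is possible, probable or definite. Concomitant therapy is among the alternative causes to be weighed.
- **Serious adverse reaction (12.1):** an event "believed to be possibly, probably or definitely due to ivermectin or any other study treatments".

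Neither safety endpoint is cut or divided at the first dose of artemether-lumefantrine.

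**The concern.** An any-AE count meant to describe ivermectin also counts whatever happens after a second active drug. Section 12.1 includes abnormal laboratory findings among AEs, and the scheduled Day 14 haematology and biochemistry follow artemether-lumefantrine in everyone who received it.

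The consequences differ by stage:

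- **Arms I-III** have five participants each and no concurrent control. An event after Day 7 adds to the ivermectin count, and no comparison within the stage can show what artemether-lumefantrine alone would produce.
- **Arm IV** gives artemether-lumefantrine to both groups. Shared events raise both proportions and shrink any real excess on ivermectin.

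For 8.3 the issue is clarity. The wording does not settle whether *related* governs Grade 3 AEs as well as SAEs, and section 12 is not consistent about what an event must be related to.

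**Working it through.** The protocol gives no figure on this point. Its formal sample size (17 events in Arm IV) concerns efficacy and has no bearing here.

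**1. Overlap of the windows.** The endpoint window is Day 0 to Day 14 (8.4, section 9). Artemether-lumefantrine is given at Day 7 at the latest (6.2.6). Days after it: 14 - 7 = 7, and 7/14 = 50% of the window. Participants rescued earlier have more.

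**2. Ivermectin remaining at Day 7.** Inputs: half-life 38.9 h (3.3) and doses at 0, 24 and 48 h (section 7, schedule of assessments). Fraction left of one dose after *t* hours: 0.5^(t/38.9). Day 7 is hour 168.

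| Dose at | Hours to Day 7 | Fraction left |
|---|---|---|
| 0 h | 168 | 0.050 |
| 24 h | 144 | 0.077 |
| 48 h | 120 | 0.118 |

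- Single dose (Arm I): about 5%.
- Three doses (Arms III and IVa): 0.050 + 0.077 + 0.118 = 0.245, about 25% of one dose's level.

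This assumes simple exponential decline and additive doses. It supports keeping observation after Day 7.

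**3. Effect in a five-person arm.** Let *q* be the proportion of participants with a new AE after artemether-lumefantrine. The protocol does not give *q*; I assume 10-40%. P(at least one of five) = 1 - (1 - q)^5.

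**4. Effect in Arm IV.** Let the any-AE proportions before artemether-lumefantrine be p1 (ivermectin) and p0 (placebo), and let *q* act independently and equally in both groups. The Day 14 proportions are 1 - (1 - p1)(1 - q) and 1 - (1 - p0)(1 - q). Their difference is (p1 - p0)(1 - q). Take p1 - p0 = 30 points, also an assumption.

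| q | P(at least one of five) | Difference at Day 14 |
|---|---|---|
| 10% | 41% | 27 points |
| 20% | 67% | 24 points |
| 30% | 83% | 21 points |
| 40% | 92% | 18 points |

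**5. What an event must be related to.** Read side by side, the protocol gives:

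- 12.1, adverse reaction: ivermectin and/or the *Plasmodium* infection.
- 12.1, serious adverse reaction: ivermectin or any other study treatment.
- 12.1, SUSAR: ivermectin.
- 12.2, intervention-related AE: the study intervention.

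Section 8.3 says only *related* and points to none of these.

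**The case against.** The strongest reply has four parts.

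**The primary endpoint already has a filter.** Section 12.2 is the operative definition of *related*, and it requires concomitant therapy to be weighed. Section 6.2.4 treats all medication other than the investigational drugs as concomitant, and 6.2.5 lists artemether-lumefantrine as rescue medication apart from the study drug. An event judged due to artemether-lumefantrine alone would normally be left out of 8.3. This stands. A reader might infer from the serious-adverse-reaction definition that such events count in the primary endpoint, but that sentence defines another term.

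**Arm IV is not clearly biased.** A reader might infer that earlier rescue on placebo would hide an ivermectin excess. Everyone remaining receives artemether-lumefantrine by Day 7 and both groups are counted to Day 14, so earlier rescue mainly moves reactions within the same window. This largely stands. Dilution remains, and the documents give no figure for a rescue imbalance.

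**Stopping the count at the first artemether-lumefantrine dose would be worse.** Under 6.2.6, rescue depends on fever, danger signs or parasitaemia, so truncation there would depend on outcome. If ivermectin works, placebo participants would be observed for less time. This stands and shapes the fix.

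**A split by period can go in the SAP, and the limits on Arms I-III are modest.** The data are already collected, 5.1 calls the Arm I-III sample size descriptive, the hold rules in 12.6 use drug-related events, and Arm IVb will show a background with artemether-lumefantrine and no ivermectin. All true, and this limits the weight of the point. But the pooled window is fixed in the protocol's own endpoint, Arm IVb is not concurrent with Arms I-III, and attribution to each drug is best recorded when the event is assessed.

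**Conclusion.** The point holds for the secondary safety endpoint. As written, 8.4 pools at least 7 of 14 days after a second protocol-prescribed drug into the ivermectin result, for every participant still in follow-up. Those who withdraw or are lost before Day 7 without rescue are the exception. Arms I-III cannot separate the two drugs by comparison. In Arm IV a 30-point difference would fall to 27-18 points, given the assumed 10-40% rate and equal, independent action in both groups.

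For 8.3 the finding is ambiguity only. The documents do not support saying that the primary safety conclusion is distorted. Nor do they support discarding the later window because little ivermectin is left: 12% is the residue of the third dose alone, and the three doses together leave about 25% of one dose's level at Day 7.

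This is a cheap improvement, not a flaw that undermines the trial.

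**What to change.** **In 8.4**, report AEs by arm in two fixed periods, alongside the Day 14 total:

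1. From the first dose of study drug (ivermectin or placebo) to just before the scheduled Day 7 artemether-lumefantrine dose. Naming both also gives Arm IVb a defined start, which the present reference to ivermectin does not.
2. From that scheduled dose to Day 14.

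Flag events that follow earlier rescue. Give person-time, or a sensitivity count ending at rescue; do not make truncation at rescue the main analysis.

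**In 8.3**, state that *related* applies to both SAEs and Grade 3 AEs and means related to ivermectin or placebo. Record attribution to artemether-lumefantrine separately.

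AE and SAE collection to Day 14 and all treatment stay unchanged.

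**Cost:** revised endpoint wording, one CRF field and one extra table. There are no extra visits or participants. The downside is that a late ivermectin reaction appears in the second period, where it is still visible and still in the Day 14 total.
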